### Primary Outcome

The primary outcome being assessed is an increase in FEER. This will be measured by comparing the percent of correctly identified facial emotion expressions from the baseline assessment task to the instructed mimicry experimental task. Additionally, the percent of correctly identified expressions will also be compared between the control condition and the intervention condition. This will provide 2 primary metrics: before-after percent improvement and control group to experimental group percent improvement.

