### Sample Size Calculation

Based on the effect sizes of 2 previous studies measuring similar constructs and similar tasks [32,35], to achieve a medium to large effect (eg, Gpower f^2^ test = 0.27) with a significance of 5% (*P*=.05) and power of 80%, a sample size of 58 will be required to demonstrate statistical significance for the primary hierarchal regression and analysis of variance (ANOVA). Given an expected attrition of 10%, a total of 64 participants will be recruited.

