### Statistical Analyses

The data will be analyzed using SPSS, Version 25. Alexithymia will be analyzed to aid in matching the AM group and ASD group on alexithymia. To ensure that the ASD and AM groups, and also the experimental and control groups, are comparable, means and standard deviations of participant characteristics will also be compared with tests of difference.

The study design is a mixed factor, 2x2x2, within-between design (see Table 2), and therefore, the most appropriate test of difference is a mixed factorial ANOVA, set up according to Table 2 with IQ, depression, and anxiety variables added as covariates. This will provide analyses of whether the instructed mimicry intervention task was effective by comparing baseline scores to posttest scores. Additionally, it will provide the ability to compare posttest scores between the control group and the intervention group. Finally, this analysis will have the additional ability to discern these differences based on group (ASD group and AM group).

In addition to the mixed factorial ANOVA, a hierarchical regression analysis will also be conducted (see Table 3) to determine the predictive ability of alexithymia on the primary outcome variable.

**Table 2 table2:** Experimental group and intervention design.

Time point	ASD^a^ group (n=~32)		AM^b^ group (n=~32)	
	Control task condition (n=~16)	Mimicry task condition (n=~16)	Control task condition (n=~16)	Mimicry task condition (n=~16)
Pretest	FEER^c^ task score	FEER task score	FEER task score	FEER task score
Posttest (the intervention task is the posttest)	FEER task score	FEER task score	FEER task score	FEER task score

^a^ASD: autism spectrum disorder.

^b^AM: alexithymia-matched general population.

^c^FEER: facial emotion expression recognition.

**Table 3 table3:** Hierarchal regression stages for analysis.

Stage	Variables
Stage 1	IQ, age, gender
Stage 2	+Autism
Stage 3	+Alexithymia
Stage 4	+Intervention

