### Hypotheses

It is hypothesized that the condition that receives the mimicry task will show significantly better emotion recognition improvement scores (posttest minus baseline); the degree of alexithymia will negatively predict baseline scores; the degree of alexithymia will predict improvement scores (posttest minus baseline); when matched on alexithymia, the general population and ASD population will not significantly differ in emotion recognition improvement scores (posttest minus baseline); and when matched on alexithymia, the AM group and ASD group will not significantly differ on baseline emotion recognition scores.

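### Improvement between conditions is the stated efficacy variable, but two models and two metrics are called primary and a posttest-only comparison is left unranked, so the single 5% level becomes about 6% to 11% depending on what counts

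*Protocol article*

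**What the plan says.** All references are to the protocol article.

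- **Hypotheses.** The efficacy hypothesis is that "the condition that receives the mimicry task will show significantly better emotion recognition improvement scores (posttest minus baseline"). Table 1 likewise gives the primary outcome as the FEER improvement score.
- **Primary Outcome.** The section describes a baseline-to-task comparison and then adds: "Additionally, the percent of correctly identified expressions will also be compared between the control condition and the intervention condition". It sums these up as two primary metrics, one before-after and one between groups, both expressed as percent improvement. It does not rank them.
- **Statistical Analyses.** A mixed factorial ANOVA (IQ, depression and anxiety as covariates) is to show effectiveness by comparing baseline with posttest. The next sentence reads: "Additionally, it will provide the ability to compare posttest scores between the control group and the intervention group".
- **Statistical Analyses, Table 3.** Beside the ANOVA, "a hierarchical regression analysis will also be conducted", with the stated purpose of examining how alexithymia predicts the primary outcome variable. Stage 4 of that regression adds Intervention to IQ, age, gender, autism and alexithymia.
- **Sample Size Calculation.** One 5% level, 80% power and f² = 0.27 give 58 participants "to demonstrate statistical significance for the primary hierarchal regression and analysis of variance (ANOVA"), raised to 64 for 10% attrition.

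**The concern.** Leaving the before-after metric aside, the randomised comparison can be read off in three ways:

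- (a) improvement, mimicry versus control, from the time-by-condition term of the ANOVA;
- (b) posttest score alone, mimicry versus control;
- (c) the Intervention step of the regression, which has a different covariate set.

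One undivided 5% level covers them. The article does not say which model decides or what standing (b) has. If a significant result on any of them in favour of mimicry can support the claim, that claim no longer carries the stated error rate. If mimicry has a moderate effect, (a) and (b) can give different answers, and the text offers no rule for that case.

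**Working it through.** **1. The plan's own figure.** For the overall test of a regression with the six predictors of Table 3, the noncentral F has λ = f² × N = 0.27 × 58 = 15.66 on 6 and 58 − 6 − 1 = 51 degrees of freedom. At α = 0.05 the power is 0.808, and 58 is the smallest N that reaches 80%. Attrition: 58 × 1.10 = 63.8, so 64. Dividing by 0.9 instead would give 65. The stated 58 is therefore reproduced with the whole 5% spent on one test.

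**2. How closely (a) and (b) are linked.** Take equal variances at both time points, standardised to 1, and a pre-post correlation ρ. The article gives no ρ, so this is an assumption.

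- Var(change) = 2(1 − ρ)
- Cov(change, posttest) = 1 − ρ
- Corr(change, posttest) = (1 − ρ)/√[2(1 − ρ)] = √[(1 − ρ)/2]

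At ρ = 0.5 this is 0.50, so the two tests are far from interchangeable. The chance that at least one is significant at two-sided 5% is one minus the bivariate normal probability that both statistics lie within ±1.96.

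**3. Null simulation.** N = 58, equal cells, 20,000 trials per ρ. Tests (a) and (b) used the ANOVA covariates with group and the group-by-condition term. Test (c) used the Table 3 predictors. The article does not fix the dependent variable of the regression, so (c) was run on improvement and on posttest.

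| ρ | Corr | (a) or (b), bivariate normal | (a) or (b), simulated | (a), (b) or (c), Stage 4 on improvement | (a), (b) or (c), Stage 4 on posttest | Any of three favouring mimicry (Stage 4 on improvement) |
|---|---|---|---|---|---|---|
| 0.3 | 0.592 | 8.78% | 8.84% | 9.98% | 10.48% | 4.89% |
| 0.5 | 0.500 | 9.07% | 8.95% | 10.14% | 10.72% | 5.20% |
| 0.7 | 0.387 | 9.35% | 8.97% | 10.01% | 10.62% | 5.02% |
| 0.9 | 0.224 | 9.62% | 9.52% | 10.76% | 11.20% | 5.43% |

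Test (a) alone ran at 4.7% to 5.3%, as it should. If only improvement counts, (a) or (c) gives about 6.2%, because the two models share an outcome and differ only in covariates.

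**4. Where the excess comes from.** At ρ = 0.5, adding the posttest-only test takes the rate from 5% to 8.95%, about 4 points. Adding Stage 4 on improvement takes it to 10.14%, a further 1.2 points. The benchmark for two independent tests is 1 − 0.95² = 9.75%, and for three 1 − 0.95³ = 14.3%. The realised rate for three tests is below its benchmark because (a) and (c) nearly coincide.

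**5. Disagreement when there is an effect.** With assumed true effects of 0.3 to 0.5 SD and ρ of 0.5 to 0.7, repeated simulations had (a) and (b) differ on significance in roughly 22% to 41% of trials.

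The before-after metric is not in these figures, since it is not a comparison between conditions.

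**The case against.** The strongest reply is that the article already says what counts. The first hypothesis, Table 1 and the closing sentence of Primary Outcome all point to improvement, and Statistical Analyses presents the mixed ANOVA as the most suitable test of difference. The posttest sentence says only what the model makes possible. It is not called primary, is tied to no hypothesis and is given no alpha of its own. The regression has an alexithymia purpose. A multiplicity rule may well sit in an SAP that is not shown.

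Much of this stands:

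- A reader might infer that no efficacy test is identified at all. The documents do not support that, because the efficacy variable is named. What is unsettled is the deciding model and the standing of the posttest comparison.
- A reader might also infer a flat 10% false-positive rate. That figure requires all three tests to count as routes to success, is two-sided although the hypothesis is directional, and depends on an unstated correlation.
- Stage 4 is not presented as an efficacy test in its own right, and it contributes only about 1 point.
- The sentence on percent correct under Primary Outcome can be read as improvement, because the section sums it up that way. The posttest-only route therefore rests mainly on the sentence in Statistical Analyses.
- The mere absence of a hierarchy in a condensed article is not a fault.

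What the reply does not remove is the wording that is present. Two models are called primary at one 5% level, two metrics are called primary, and a between-condition posttest comparison is set beside the improvement hypothesis. These statements do not agree on one deciding test, and an SAP would have to depart from some of them to restore 5%.

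**Conclusion.** The concern holds in a limited form. The article names improvement between conditions as the efficacy variable, then leaves other routes to the same claim open at one undivided 5% level. Under the null, the two-sided chance of at least one significant between-condition result is about 6% on the narrowest reading (improvement only, ANOVA plus Stage 4). It is about 9% with improvement and posttest alone, and about 10% to 11% with all three. In the direction of mimicry, the last is about 5% against 2.5%. Most of the excess comes from the posttest-only comparison.

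The figures assume N = 58, equal cells, equal variances at both time points and a pre-post correlation of roughly 0.3 to 0.8; the range is similar at 0.9. The disagreement rates additionally assume true effects of 0.3 to 0.5 SD. This is an ambiguity in the main randomised comparison that should be corrected by wording. It is not a defect in the design or in the sample size arithmetic.

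**What to change.** - **Statistical Analyses:** name one deciding test, the mimicry-versus-control difference in FEER improvement (the time-by-condition term of the mixed ANOVA), at two-sided 5%. Label the posttest-only comparison descriptive and regression Stage 4 supportive.
- **Primary Outcome:** keep the between-condition improvement as the single primary metric and label the before-after metric descriptive.
- **Sample Size Calculation:** remove the word primary from the regression, which stays for the alexithymia questions.
- **Hypotheses:** label all but the first as secondary.

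The cost is text only. The Timeline section reports that recruitment had not begun as of June 2021, and the sample size is unchanged. The price is that a significant posttest-only, before-after or Stage 4 result can no longer carry the efficacy claim by itself.

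Splitting alpha would be dearer. On the plan's own six-predictor calculation, power at N = 58 falls from 0.81 to 0.71 at α = 0.025, or 0.66 at α = 0.05/3. Restoring 80% would need 67 or 72 evaluable participants.

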### Assessments

The main aim of the current study is to assess the efficacy of the intervention in the general population and an ASD population, but also if people with high levels of alexithymia gain additional benefit. Further, this study will aim to replicate the study by Cook et al [32], which suggested that alexithymia, not ASD, predicts poor FEER. This requires having a general population group and another group with people with ASD, with both groups being matched on levels of alexithymia. Therefore, participants will be prescreened online to facilitate creating this composition of participants. During the online screening stage, participants will choose to consent in the study, complete the TAS-20, and indicate if they have an ASD or if they have been diagnosed with an ASD. During this screening stage, participants will also complete demographic information, the Autism Spectrum Quotient (AQ-10) [42], and the K-10.

Participants will then be invited to a clinical interview with a provisional psychologist (PP) at the Federation University Psychology Clinic who will confirm a reported diagnosis of ASD and complete an observational assessment that gives a diagnostic indication of an ASD. Participants who have reported a diagnosis will be asked what instrument was used and if the PP can request a copy of the results. The PP will also complete the Autism Mental Status Exam 2.2 (AMSE) [43,44]. The AMSE is an 8-item observational assessment that takes place during a clinical interview and predicts ASD classification on the Autism Diagnostic Observation Schedule (ADOS) [45]. During this clinical interview, participants will also be administered the Depression Anxiety Stress Scales-21 (DASS-21) [46] and the Wechsler Abbreviated Scale of Intelligence (WASI-II) [47] to assess depression, anxiety, and IQ, which will be used as control variables in the analyses of the results.

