### Comparator/Control Group

This study includes both a before-after, within-group comparator and a between-groups control group. To make the before-after comparison, participants will first partake in a baseline assessment task of emotion recognition before randomization to one of the experimental conditions. This baseline assessment task will be the same as the intervention task; however, participants will not be instructed to mimic the facial expressions prior to selecting an expression.

In addition to the before-after comparator, there will be a control condition. The control condition will also undergo the baseline assessment task; however, instead of participating in the mimicry intervention task, they will undergo a similar task with no mimicry element. This task will be identical to the instructed mimicry intervention task; however, instead of being instructed to mimic the facial expression, they will be instructed to “pay particular attention to the entire face prior to selecting an expression.” This instruction is aimed to match for attention levels.

A final point of comparison will be that participants will be first broken up into 2 groups, namely the AM group and ASD group. This comparison will provide the ability to analyze if any intervention effects only occur or are stronger in people with ASD, alexithymia, or the general population. The participant flow diagram can be seen in Figure 3.

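### The aim of showing extra benefit in people with high alexithymia has no matching model term, and the hypothesis that alexithymia predicts baseline recognition has no listed model

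*Protocol article*

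**What the plan says.** Two sections of the protocol article set a moderation question. Assessments puts efficacy in the two populations first and then adds "but also if people with high levels of alexithymia gain additional benefit". Comparator/Control Group says the design will allow the team to "analyze if any intervention effects only occur or are stronger in people with ASD, alexithymia, or the general population".

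Statistical Analyses lists two models.

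- **Mixed factorial ANOVA (Table 2):** time by task condition by ASD/AM group, with IQ, depression and anxiety as covariates. Alexithymia is neither a factor nor a covariate.
- **Hierarchical regression (Table 3):** described as "a hierarchical regression analysis will also be conducted (see Table 3) to determine the predictive ability of alexithymia on the primary outcome variable". The stages are IQ, age and gender; then Autism; then Alexithymia; then Intervention. No product term is listed.

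The Primary Outcome section defines the primary outcome as an increase in FEER, and Table 1 lists an improvement score as its instrument. Hypotheses includes one on baseline level, "the degree of alexithymia will negatively predict baseline scores", and a separate one that alexithymia predicts improvement.

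**The concern.** Whether mimicry works better in people with high alexithymia is a question about a difference between two slopes: alexithymia against change under mimicry, and alexithymia against change under the control task. Neither model estimates that difference. The ASD/AM factor cannot stand in for alexithymia, because the two groups are to be matched on the number of participants with TAS-20 scores of 61 or more.

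The risk is one of interpretation. The plan expects people high in alexithymia to start lower, and percent correct is bounded. If low scorers gain more from ordinary practice, alexithymia can predict improvement in both arms alike. A reader could take that coefficient as selective benefit from mimicry when the control arm shows the same pattern.

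Separately, if the only regression is on improvement, no listed model relates alexithymia to baseline FEER. The hypothesis on baseline level and the alexithymia half of the second study aim then have no stated test.

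**Working it through.** **1. The plan's own sample size.** Inputs from Sample Size Calculation: f² = 0.27, alpha 0.05, power 80%, and "a sample size of 58 will be required to demonstrate statistical significance for the primary hierarchal regression and analysis of variance (ANOVA". For an overall regression test with p predictors, the noncentrality is λ = f²·N and the error df is N − p − 1.

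- p = 6 (the six main effects of Table 3), N = 58: λ = 0.27 × 58 = 15.66, df 6 and 51, power 80.8%. N = 57 gives 79.9%. The stated 58 is reproduced exactly.
- p = 7 (one product term added): N = 61.

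The sizing therefore fits Table 3 as printed, with no interaction.

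**2. What the planned coefficient estimates.** Let b_C and b_M be the slopes of change on alexithymia in the control and mimicry arms. With equal arms and similar alexithymia spread, the Table 3 coefficient is about (b_C + b_M)/2. The moderation question is b_M − b_C. Illustrative simulation at N = 58, standardized alexithymia, residual SD 1, with the six Table 3 predictors:

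| b_C | b_M | b_M − b_C | Planned term significant | Interaction significant |
|---|---|---|---|---|
| 0.5 | 0.5 | 0 | 93% | 5% |
| −0.4 | 0.4 | 0.8 | 6% | 78% |
| 0 | 0.8 | 0.8 | 73% | 79% |

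The planned term is usually significant in row 1, where there is no differential benefit, and in row 3, where there is. It almost never is in row 2, where there is also a differential benefit.

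**3. Could it be significant with no mimicry effect?** This depends on quantities the documents do not give: baseline mean, the correlation of alexithymia with ability, the spread of ability, and the practice gain. Simulations with N = 64, 36 six-choice trials, the same practice process in both arms and no mimicry effect gave:

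| Assumed correlation | Assumed baseline | Practice gain (points) | Alexithymia term significant |
|---|---|---|---|
| −0.5 | 75–83% | 6–12 | 19–58% |
| −0.5 | about 76–80% | 7–11 | 14–59% |
| −0.5 | 74–83% | 7–9 | 10–25% |
| −0.3 | 74–83% | 7–9 | 7–12% |
| −0.3 or −0.5 | 74–83% | 2–5 | about 5–8% |

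The last three rows assume a logit-scale ability SD of 0.5 to 0.8 and a common logit shift. The spread is not specified for the first two, so the rows do not differ in gain alone. A further set gave about 6 to 41%, near nominal for gains of about 4 points. The interaction test, where run (first two rows), rejected in about 4 to 6%.

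**4. What the added term can detect.** With equal arms and standardized alexithymia, the SE of the slope difference is about 2/√58 = 0.263 residual SD, with 58 − 7 − 1 = 50 df. A difference of 0.75 gives 0.75/0.263 = 2.86 and power 80%. Equivalently, f² = 0.75²/4 = 0.141. At N = 64 the limit is f² = 0.127, a difference of 2 × √0.127 = 0.71.

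For smaller interactions, power at N = 58 is 66% at f² = 0.10, 39% at 0.05 and 18% at 0.02. The formula is slightly optimistic: it gives about 85% for a difference of 0.8, where the simulation in step 2 gave 78 to 79%.

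**5. Hypotheses against listed models.**

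- *Mimicry improves more than control:* ANOVA time by condition.
- *Alexithymia predicts improvement:* Table 3, Stage 3.
- *ASD and AM groups do not differ in improvement:* ANOVA time by group.
- *ASD and AM groups do not differ at baseline:* pretest level of the ANOVA.
- *Alexithymia negatively predicts baseline:* no listed model, if the regression outcome is improvement.

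**The case against.** **No stated hypothesis needs an interaction.** This is correct. The hypothesis that alexithymia predicts improvement is a main effect, and Stage 3 tests it. The gap is between the models and the questions posed in Assessments and Comparator/Control Group.

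**Detail may be left to a fuller plan.** This would hold if the article were silent on model terms. Tables 2 and 3 list them, so this is a stated analysis that does not answer a stated question.

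**The regression outcome is not named as improvement.** Statistical Analyses says only that it is the primary outcome variable, and Table 1 gives the concept as FEER ability measured at pretest and during the task. A baseline run of Stages 1 to 3 may be intended. Improvement is the likelier reading, given the Primary Outcome section and the instrument named in Table 1, but the ambiguity is real and is itself a reason to name the outcome.

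**Practice gains may be small.** The Intervention section describes no correctness feedback. With gains of 2 to 5 points the error rate stays near nominal, and a gain equal in percentage points away from the ceiling would create no bias of this kind. This stands. A reader might infer that alexithymia is bound to predict improvement even if mimicry does nothing; the documents do not support that.

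**The ASD question is already covered.** This also stands. The ANOVA's time by condition by group term addresses a different mimicry effect in the ASD group, so an Autism by Intervention term is not missing.

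**Conclusion.** The concern holds in a limited form. As planned, no coefficient estimates whether the mimicry effect varies with alexithymia, and the Stage 3 coefficient cannot support a claim of additional benefit. That follows from the listed terms and needs no numerical assumption. How often the coefficient would mislead does rest on assumptions: roughly 5 to 60% significance across the simulations with no mimicry effect, and about 5 to 10% for practice gains of 2 to 5 points.

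On the likelier reading of the regression outcome, one of the two baseline hypotheses has no listed model. A reader might infer that both are untestable, but the ASD versus AM comparison is available from the ANOVA. A reader might also infer that the trial can never address moderation; alexithymia and baseline FEER are both collected, so the limitation lies in the analysis plan only. The main comparison of mimicry with control is unaffected.

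**What to change.** 1. Add a Stage 5 to Table 3 with centred alexithymia by Intervention, keeping both main effects. Base any statement about additional benefit in alexithymia only on that coefficient and its confidence interval. Describe the Stage 3 coefficient as an association with improvement pooled over both tasks.
2. Name the regression outcome, and run Stages 1 to 3 a second time with baseline FEER as the outcome, as the test of the baseline alexithymia hypothesis.
3. State the detectable interaction: about 0.75 SD of change per SD of alexithymia at N = 58 (f² about 0.14). Say that a null result is not evidence of no moderation.

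The cost is one model term, one extra regression run and one error degree of freedom (51 to 50), with no new data. The overall regression test at f² = 0.27 would need 61 rather than 58. The real price is modest power for the interaction, which has to be declared. The changes should be fixed before outcome data are examined, since a term added afterwards would be post hoc.

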### Participants

We will recruit through local ASD support groups, online social media, and noticeboard advertisements (eg, at Federation University Australia). We will also use snowball recruiting to better penetrate the ASD community. Participants with an ASD (based on the assessments described in the Assessment section) will be assigned to the ASD group. Other participants will be assigned to the alexithymia-matched general population group (AM group).

The researchers will also use the 20-item Toronto Alexithymia Scale (TAS-20) total scores [40] to match the ASD group with the AM group without an ASD. Specifically, the number of participants in each group meeting criteria for alexithymia will be matched as indicated by TAS-20 scores ≥61, which is how groups have been matched in similar studies (eg, [32]).

The inclusion criterion is that participants are 18 years of age and older. The ASD group also has the added inclusion criterion of a confirmed ASD based on the assessment described in the Assessment section. Exclusion criteria include the participant having another mental health condition (other than an ASD if in the ASD group) diagnosed by a clinician and that the Kessler Psychological Distress Scale (K10) [41] indicates a significant level of distress (cut-off score of 22).

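### Table 3, the only specified model that tests alexithymia, omits the depression and anxiety control variables that the plan promises, leaving the alexithymia coefficient open to confounding

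*Protocol article*

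**What the plan says.** All references are to the protocol article.

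- **Assessments** says that the DASS-21 and WASI-II are given "to assess depression, anxiety, and IQ, which will be used as control variables in the analyses of the results". The commitment is general and not tied to one model.
- **Statistical Analyses, ANOVA:** the mixed factorial ANOVA is run "with IQ, depression, and anxiety variables added as covariates". Table 2 sets it up by ASD/AM group, task condition and time, with no alexithymia term.
- **Statistical Analyses, Table 3:** the plan says that "a hierarchical regression analysis will also be conducted (see Table 3) to determine the predictive ability of alexithymia on the primary outcome variable". Stage 1 holds IQ, age and gender. Later stages add autism, alexithymia and intervention. Depression and anxiety appear at no stage.
- **Hypotheses:** two of the five concern alexithymia as a predictor. The second is that "the degree of alexithymia will negatively predict baseline scores". The third is that "the degree of alexithymia will predict improvement scores (posttest minus baseline"), with no direction given.
- **Sample Size Calculation** calls the regression primary and gives 58 analysable participants (64 recruited) for f² = 0.27, 5% significance and 80% power.
- **Table 1** lists the DASS-21 under eligibility, not under control variables.

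**The concern.** The two covariates are placed where validity needs them least and left out where it needs them most. Mimicry versus control is randomised, so that contrast is unbiased without them. Alexithymia is a measured trait. If depression or anxiety is related both to alexithymia and to facial emotion recognition, an unadjusted alexithymia coefficient takes up part of their effect.

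The second and third hypotheses, and the alexithymia half of the second study aim, rest on that coefficient. An effect of mood on recognition could be reported as support for the alexithymia hypothesis, although the trial will hold the DASS-21 data needed to separate the two.

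**Working it through.** **1. Covariates side by side**

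| Place | IQ | Depression | Anxiety | Alexithymia tested? |
|---|---|---|---|---|
| Assessments (commitment) | yes | yes | yes | – |
| ANOVA (Table 2 and text) | yes | yes | yes | no |
| Regression (Table 3, all stages) | yes | no | no | yes |

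**2. The plan's own sample size**

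For the overall regression test with p predictors, the noncentrality is λ = f²·N, with p and N − p − 1 degrees of freedom. With f² = 0.27, N = 58 and p = 6, λ = 15.66 and power is 80.8%; at N = 57 it is 79.9%. So 58 is reproduced with six predictors, which is the Table 3 count (IQ, age, gender, autism, alexithymia, intervention). For this overall test no other p from 1 to 9 gives 58. Adding 10% gives 58 × 1.10 = 63.8, or 64.

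This suggests that the regression was sized without the two covariates, but does not prove it: a test of six predictors added to two others also needs 58 (power 80.6%).

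**3. Size of the possible bias (baseline outcome)**

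Assume standardised variables, one depression/anxiety composite and no true alexithymia effect. Let r be the correlation of alexithymia with depression, and b the effect of depression on recognition. The spurious alexithymia slope is r × b. The documents give neither value, so both are assumed.

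The rejection rate follows from f² = (rb)² / [1 − (rb)²] and λ = f²·N with 1 numerator degree of freedom. For example, r = 0.3 and b = −0.2 give rb = −0.06, f² = 0.0036, λ = 0.21 and 7.3% rejection at N = 58.

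| r | b | spurious slope | formula, N = 58 | simulation, N = 58 | simulation, N = 64 |
|---|---|---|---|---|---|
| any | 0 | 0 | 5% | – | – |
| 0.3 | −0.1 | −0.03 | 5.6% | – | – |
| 0.3 | −0.2 | −0.06 | 7.3% | – | – |
| 0.3 | −0.3 | −0.09 | 10.4% | 10.0% | 11.0% |
| 0.3 | −0.4 | −0.12 | 14.7% | 14.7% | 14.7% |
| 0.5 | −0.3 | −0.15 | 20.5% | 19.2% | 20.6% |
| 0.5 | −0.4 | −0.20 | 33.2% | 30.8% | 33.5% |

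The simulation used 6,000 runs per cell, regressing recognition on IQ, age, gender, ASD and alexithymia. With depression and anxiety added, rejection was 4.6% to 5.3% throughout. No range restriction was applied. A positive b reverses the sign: r = 0.6 and b = +0.2 give +0.12.

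**4. Power after adding the two covariates (eight predictors)**

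- Overall test, f² = 0.27: power at 58 is 74.5%. It needs 64 analysable (80.2%), so 64 × 1.10 = 70.4 (71 recruited) or 64 / 0.90 = 71.1 (72 recruited).
- Single alexithymia test, f² = 0.27, N = 58: 97.3% with six predictors. With eight it is 97.2% if depression and anxiety explain none of alexithymia's variance. If they explain 40% (assumed), f² becomes 0.27 × 0.6 = 0.162 and power 85.2%.

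**The case against.** A reader might infer that the coefficient **is** confounded, and towards the hypothesis. The documents do not support that. It needs a positive correlation of depression or anxiety with alexithymia and a negative effect on recognition, and neither is given. With no effect on recognition there is no bias; with a positive one it runs the other way. The third hypothesis has no direction, so the inference could apply only to the second.

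Four further points limit the size:

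- The calculation is for a recognition level, in effect baseline. The primary outcome is improvement, and a stable effect of depression on level would largely cancel from posttest minus baseline. Bias there needs its own assumption.
- Participants with another clinician-diagnosed mental health condition, or with a K-10 score indicating significant distress, are excluded. This narrows the range. If the K-10 correlates 0.6 to 0.8 with depression and the lowest 50% to 85% are kept (both assumed), the formula result for the strongest cell falls from 33% to 17–28%, and the r = 0.3, b = −0.3 cell from 10% to 7–9%. The bias shrinks but does not vanish.
- The ANOVA adjusts the non-randomised ASD versus AM contrast for depression and anxiety, so the second aim does not rest on the alexithymia coefficient alone.
- If depression were a consequence of alexithymia, adjustment could remove part of the effect of interest. The plan makes no such argument and itself calls these control variables; reporting both models covers it.

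These points stand and limit the claim. They do not remove the contradiction. Nor can it be put down to a condensed article, because Table 3 is a complete stage-by-stage list.

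**Conclusion.** The point holds as an internal contradiction with a real exposure. The plan promises control for depression and anxiety, provides it in the ANOVA, and omits it from the only specified model that tests alexithymia. The coefficient behind the second and third hypotheses is therefore open to confounding. The bias would favour the baseline hypothesis if depression and anxiety rise with alexithymia and lower recognition, which the documents do not establish.

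For a baseline outcome, the false-positive rate of the nominal 5% test runs from 5% with no effect of depression, through about 5.5% to 7.5% (r = 0.3, b = −0.1 to −0.2), to about 30% to 34% (r = 0.5, b = −0.4). All of these rest on assumed correlations, one composite confounder and no range restriction. No figure is offered for the improvement score. The plan should be corrected, because the remedy uses data already to be collected and follows its own commitment.

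**What to change.** - Change Table 3, Stage 1, to: IQ, age, gender, DASS-21 depression, DASS-21 anxiety, in every regression that tests alexithymia. If the sponsor prefers to leave them out, justify the departure from the Assessments section.
- Report the model without them as a sensitivity analysis.
- List the DASS-21 under control variables in Table 1.
- Restate the Sample Size Calculation. Either give the overall test with eight predictors (74.5% power at 58; 64 analysable needed for 80%), or state power for the single alexithymia test (about 85% to 97% at f² = 0.27, for 40% down to 0% of its variance explained by depression and anxiety).

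**Cost:** no new data, two degrees of freedom and a somewhat wider alexithymia interval. Before any gain from lower residual variance, the widening factor is 1/√(1 − R²), where R² is the share of alexithymia's variance that the covariates explain. That is about 5% for R² = 0.09 (r = 0.3), 15% for 0.25 (r = 0.5) and 29% for 0.40. If the overall test is kept as the basis at 80% power, recruitment would rise from 64 to 71 or 72; basing the statement on the single alexithymia test avoids this.
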